#### Schedule of assessment part 2:

In summary: Nine patients in total are foreseen to participate in part 2 of the trial. These 9 patients will all receive the MSD during 8 weeks. Between 28 days and one day before the start of the trial for them, patients will be screened if they qualify for the participation in the trial. If all eligibility criteria are fulfilled, patients will be enrolled to the trial and trial specific procedures will start. During week 1, patients have to show up every day at the CI Bern. CI Bern is a clinical trial unit providing facilities and services to support clinical trials and serves as satellite site. CI Bern was chosen in order to perform PK sampling and assessments. As of week 2, patients will only have one visit per week, where treatment (TLN infusion) and assessments will take place at the same time. These visits will take place in the Institute of Neurology in Konolfingen. All patients will continue in the same manner and receive a weekly infusion of TLN until criteria are met to stop the treatment.

Patients from the part 1 of the trial, wishing to take the option of continuing the treatment will follow the same schedule as the patients of part 2 (see schedule of assessment above) with the exception of the PK sampling, and baseline (the data will be added to part 1). All assessments will take place in the Institute of Neurology in Konolfingen.

| Trial Periods                 | Re-consent | T | T | T  | T  | T  | T  | T  | T  | Final assessment | Follow-up |
|-------------------------------|------------|---|---|----|----|----|----|----|----|------------------|-----------|
| Visit                         | 0          | 1 | 2 | 3  | 4  | 5  | 6  | 7  | 8  | 9                | 10        |
| Time (weeks)                  | -4 to -1   | 1 | 2 | 3  | 4  | 5  | 6  | 7  | 8  | +1               | +4        |
| Time (days)                   | -28 to 0   | 1 | 8 | 15 | 22 | 29 | 36 | 43 | 50 | +7               | +28       |
| Patient information & consent | x*         |   |   |    |    |    |    |    |    |                  |           |
| Clinical Assessment           |            |   |   |    |    |    |    |    |    | x                | x         |
| Vital Signs                   |            | x | x | x  | x  | x  | x  | x  | x  | x                | x         |
| MoCA                          |            |   |   |    |    |    |    |    |    | x                |           |
| Lab tests                     |            | x | x | x  | x  | x  | x  | x  | x  | x                | x         |
| Levodopa Challenge Test       |            |   |   |    |    |    |    |    |    | x                |           |
| TLN Infusion                  |            | x | x | x  | x  | x  | x  | x  | x  |                  |           |
| Blood collection (PK)         |            |   |   |    |    |    |    |    |    |                  |           |
| MDS-UPDRS                     |            | x | x | x  | x  | x  | x  | x  | x  | x                | x         |
| PDQ-39                        |            |   |   |    |    |    |    |    |    | x                |           |
| ESS                           |            |   |   |    |    |    |    |    |    | x                |           |
| BDI                           |            |   |   |    |    |    |    |    |    | x                |           |
| SAS                           |            |   |   |    |    |    |    |    |    | x                |           |
| NMSQuest                      |            | x | x | x  | x  | x  | x  | x  | x  | x                |           |
| LEDD                          |            | x | x | x  | x  | x  | x  | x  | x  | x                | x         |
| Adverse events recording      |            | x | x | x  | x  | x  | x  | x  | x  | x                | x         |

Schedule of assessment prolongation (optional): \*Patient consent for the treatment prolongation might also be collected at the final assessment or follow-up visit of the schedule of part 1.

## 9.2 Assessments of outcomes

### 9.2.1 Assessment of primary outcome

Clinical AEs, lab values and vital signs, will be assessed during each visit as reflected in the two schedules (part 1 and part 2 of the trial). In addition, patients will also be asked to contact the PI's practice if they experience any adverse effect between visits, to assess if this could be related to the treatment and would require further medical attention and if any actions are to be taken. Patients will be asked to provide as much detail as possible at the time of the visit. Details should include the time and duration of these occurrences that will be examined with the investigator to fill the weekly reporting of AE. The investigator will document the AEs in the eCRF after each visit and will notify the sponsor in case of SAEs. All AEs and SAEs will be documented as follows: time of onset, duration, resolution, action to be taken, assessment of intensity, relationship with trial treatment (for all details refer to section **10 SAFETY**). Pre-existing signs and symptoms, especially of PD, are not to be considered an AE. Parkinsonian signs and symptoms are considered an AE in this trial if they appear to be new or if a previously present non-fluctuating symptom clearly worsens. A fluctuating parkinsonian symptom will only be counted as an AE if the fluctuation clearly increases in frequency or duration or if the extent of the fluctuating symptom at its worst is clearly worse compared to the baseline condition.

In order to assess other safety issues, blood samples will be taken and analysed for routine assessments (termed full lab tests thereafter) to assess if TLN modifies the blood cell count, the electrolytes, metabolites and liver markers (for the full list of lab tests and standard values see the **Annexes 1 & 2**) or result in an elevation of anti-GM1 antibodies or apolipoprotein B (a marker of hyperlipidaemia).

The full lab tests consist of:

- 1- The "routine" lab analyses will be performed (Cat #: Rout-3549)
- 2- Anti-GM1 IgG antibodies (Cat #: gm1g 52250)
- 3- Apolipoprotein B (Cat #: apob-7320) assays

All required material will be provided by Viollier. 4 tubes (3 x 0.5 ml of blood serum-gel-tube and 1 x 0.5 ml of blood in EDTA tube) will be required for these tests from each patient.

Safety lab values will be assessed from blood collection performed every week during part 1 (3 days after TLN infusion) and part 2 (on the day of TLN infusion) according to the schedule. Abnormal

values will be compared to the normal range provided by the laboratory (**Annex 2**), then assessed by the PI for grading. All analyses will be performed from venous blood collection before the infusion. Samples will be collected on each sampling day by courier by Viollier and processed in their facilities.

### 9.2.2 Assessment of secondary outcomes

- Cognitive assessment: Montreal Cognitive Assessment (MoCA): The MoCA is a short screening test for the detection of cognitive impairment and dementia. The test will take approximately 15 min in cognitively unimpaired participants.
- Levodopa challenge test (LCT): The LCT will be performed in a “defined off” because “worst off” cannot be obtained within reasonable time. All PD medications are stopped at least 12 h before the test. A motor assessment (MDS-UPDRS-3) is performed in this defined “off” state. Then the LED of the morning medication plus 50 mg of levodopa is given p.o. as soluble levodopa (Madopar liquid). The motor assessment is then repeated 1 h later. Usual daily medication is resumed after the LCT. In total the test lasts for maximally 2 h.
- MDS-UPDRS: The MDS-UPDRS consists of four parts: Part I (experiences of daily life - non-motor aspects), Part II (experiences of daily life - motor aspects), Part III (motor examination) and Part IV (motor complications). Part I consists of two components: Part Ia relates to various behavioural problems that the PI will evaluate using the information available from the patient and the caregiver (if available). Part Ib should be completed by the patient with or without the support of the caregiver, but independently of the PI. However, this part can be checked by the PI in order to ensure a clear and unambiguous answer to the questions. The investigator can also help to explain any uncertainties. Part II, like Part Ib, is designed as a self-questionnaire, but Part II can also be checked by the PI for completeness and freedom from errors. Part II will be assessed for best and worst condition in the previous week in patients with fluctuating parkinsonian signs and symptoms. Part III contains instructions for the PI, which are read to the patient or demonstrated directly; this part is completed by the PI as a motor examination. Part IV contains instructions for the investigator and also instructions that must be read to the patient. This part combines patient-related information with the clinical observations and assessments of the examiner and is therefore also filled out by the examiner. To investigate if the infusion has an immediate motor effect on the patient's condition, Part III will be repeated before and after the infusion. The questionnaires of the MDS-UPDRS (parts 1, 2 and 4) will take up to 1 h; for this study, these parts that refer to the previous week will be assessed in an interview with the patient to guarantee accurate responses.
- Parkinson's Disease Questionnaire 39 (PDQ-39): Difference in the PDQ-39 summary index between baseline assessment and the final assessment (1 week after the last TLN infusion). The PDQ-39 is a disease-specific questionnaire for quality of life of the affected patients. The 39 items are subdivided into 8 subscales: mobility, daily activity, emotional well-being, stigma, social support, cognition, communication, physical discomfort. Patients will be asked to complete the questionnaire by using the five categories for their answers that are foreseen with a coding from 0-4 (0 = «niemals»; 1 = «selten»; 2 = «manchmal»; 3 = «häufig»; 4 = «immer oder kann ich überhaupt nicht»). The completion of the questionnaire will take the patients 5 to 10 min.
- Epworth Sleepiness Scale ESS): The ESS is a questionnaire to help measure the general level of daytime sleepiness. Patients are to rate the chance that they would doze off or fall asleep during eight different routine daytime situations. Each item is rated from 0 to 3 (0 = “würde niemals einnicken”; 1 = “geringe Wahrscheinlichkeit einzunicken”; 2 = “mittlere Wahrscheinlichkeit einzunicken”; 3 = “hohe Wahrscheinlichkeit einzunicken”). The completion of the questionnaire will take the patients approximately 5 min.
- Assessment of mood using the Beck Depression Inventory (BDI): Patients will be asked to complete the 21 questions on how they felt during the last week. Four options for their answer are foreseen (e.g. “ich bin nicht traurig”, “ich bin traurig”, “ich bin die ganze Zeit traurig und komme nicht davon los», «ich bin so traurig oder unglücklich, dass ich es kaum noch ertrage»). The completion of the questionnaire will take the patients 5 to 10 min.
- Motivation assessment by the Starkstein Apathy Scale (SAS): Patients will be asked to complete the 14 questions concerning their interest and motivation for certain activities. Four options for their answer are foreseen (“überhaupt nicht”, “ein wenig”, “ziemlich viel”, “sehr viel”). The completion of the questionnaire will take the patients 5 to 10 min.

- Non-Motor Symptoms Questionnaire (NMSQuest): This questionnaire enables clinicians to complete a comprehensive assessment of a diverse range of non-motor symptoms which can occur in all stages of PD. It is a patient-based screening tool designed to draw attention to the presence of non-motor symptoms in patients for further investigation or treatment. Patients will be asked to give their answer ("ja" or "nein") to 30 questions.
- Levodopa equivalent daily dose (LEDD): LEDD will be assessed at each visit and will be calculated according to Verber *et. al*.
- Pharmacokinetics (PK) of total GM1 in blood over the first 96 h after the first infusion (only in part 2 of the trial):  
The assessment of PK will be determined by the calculation of the Maximum Observed Drug Concentration ( $C_{max}$ ) in plasma, the Time of Maximum Drug Concentration ( $T_{max}$ ) in plasma,  $AUC_{inf}$  in plasma, half-life ( $t_{1/2}$ ) Clearance (CL) and the volume of distribution ( $V_d$ ).  
The predicted half-life of the drug is 30 h according to our pre-clinical data obtained in animals. The blood collection for PK will therefore be performed at the following timepoints after the first infusion (only part 2 of the trial):
  - 0 min (right before the infusion, pre-dose)
  - 5 min before the end of the infusion
  - 30 min after infusion
  - 1 h after infusion
  - 4 h after infusion
  - 24 h after infusion
  - 48 h after infusion
  - 72 h after infusion
  - 96 h after infusion
 Instructions for the collection of blood and the processing and handling are provided in **Annex 3**).
- Determine the maximal suitable dose (MSD): MSD is calculated as the average dose from all maximally reached doses by the 3 patients in the dose escalating part of this trial.

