| Clinical Phase:              | Phase I, Safety evaluation                                                                                                                                                                                                                                                                                                                                                                                                                                                                          |
| Background and Rationale:    | The pharmacologically active ingredient of TLN is the membranal lipid Monosialotetrahexosylganglioside or GM1. TLN consists of GM1 associated to a proprietary lipid formulation assembled together as liposomes. Free injections of GM1 have shown to improve the UPDRS-score and therefore the condition of patients with Parkinson's disease. TLN has been developed to improve the delivery of GM1 and its bioavailability and therefore improve the care of Patients with Parkinson's disease. |
| Objective(s):                | The primary objective is: 
 
To demonstrate the safety of TLN administration intravenously in patients with Parkinson's disease.
 
 Secondary objectives are: 
 
Determination of the maximal suitable dose based on safety profile and preliminary efficacy.
 
Determination of the PK profile.
 
                                                                                                  |
| Outcome(s):                  | Primary outcome: Safety, measured as: 
 
Occurrence of AEs
 
Occurrence of SAEs
 
 Secondary outcomes: 
 
Parkinson disease (PD) patients' condition assessed by: Levodopa challenge test (LCT), MDS-UPDRS, PDQ-39, ESS and change in Parkinson's medication (LEDD).
 
Patients' general/mental condition assessed by: BDI, SAS, NMSQuest and MoCA.
 
PK analyses
 
     |

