#### 6.1.1 Dose escalation (Part 1)

In this part a group of 3 patients will receive a single weekly dose that will be increased according to the schedule defined. In parallel, meaning that the first patient will receive a dose X on week Y, if the safety assessment is positive (see **Section 8.3 Dose modifications**) then the following week (Y+1) this patient will receive the next dose (X+1), on that week (Y+1) two other patients will receive the same dose X to confirm the safety assessment. *In fine*, every week patient 1 will receive one dose at the same time that patients 2 & 3 receive the preceding dose.

This weekly increase has been elected to allow rapid determination of the MSD and rapidly reach a dose level that will be beneficial for the patients involved in this trial. This is allowed by the fact that GM1 is expected to be safe and no clear AE are foreseen within this dose range. Furthermore, the 1 + 2 pattern allows one week observation of each dose increase in 1 patient before infusing 2 more.

The first dose level starts at 6 mg which will increase to 12 and 60 mg, then increasing by equal steps of 60 mg up to 720 mg. The escalation will be stopped individually according to the decision matrix detailed in the **Section 8.3 Doses modifications**. The three first steps of the dose are purposely low to account for any possible unexpected effects of the formulation.

Throughout the escalation part, all patients will be monitored twice weekly to record AEs and document them. Monitoring will take place once before each TLN infusion (beginning of the week) and a second time by the end of each week (performed by the principal investigator) to collect AE and allow enough time for the IMC to review them and take their decision on the next infusion/dose modification/delay.

At the end of the escalation, the average of the three maximum tolerated doses by the three patients will be defined as MSD for part 2. With this design, we aim to find the highest dose that generates, if any at all, at maximum only transient mild/moderate AEs. At the same time, this will allow to glean information on clinical effect for the planning of a potential phase II study.

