### 8.3 Dose modifications

Dose modifications are foreseen in cases where a causal relationship to the treatment with TLN cannot be excluded. A causal relationship in this trial is defined as a possible, probable or definite linkage to TLN according to ICH E2A (for more details see section **10. Safety**).

Any grade 4 event with causal relationship to treatment is judged as unacceptable toxicity and will lead to a stop of treatment without resuming the treatment in the affected patient.

Any SAE leads to a treatment stop for the affected patient with the following exception:

- if there is no causal relationship to TLN and the definition for an SAE is fulfilled **uniquely due to an overnight hospital stay (1 night) for an otherwise not severe or serious medical problem**, the patient can continue study participation.

In case of an SAE with no causal relationship to TLN, the patient will be replaced.

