#### Part 1 – Dose escalation:

| Causality            | Intensity   | Resolution until next infusion | Next patient added/ Dose increase                                                                                                         |
|----------------------|-------------|--------------------------------|-------------------------------------------------------------------------------------------------------------------------------------------|
| (unlikely/unrelated) | grade 1 - 3 | yes/no                         | yes                                                                                                                                       |
| Possible             | grade 1     | yes                            | yes                                                                                                                                       |
| Possible             | grade 1     | no                             | yes                                                                                                                                       |
| Possible             | grade 2     | yes                            | yes                                                                                                                                       |
| Possible             | grade 2     | no                             | Delay till resolution (maximum of 3 weeks), then rechallenge at same dose level, if re-occurrence stop treatment for the affected patient |
| Possible             | grade 3     | yes/no                         | no (stop treatment for the affected patient but others to continue)                                                                       |
| Probable/definite    | grade 1     | yes/no                         | yes                                                                                                                                       |
| Probable/definite    | grade 2     | yes                            | yes                                                                                                                                       |
| Probable/definite    | grade 2     | no                             | no (stop treatment for the affected patient but others to continue)                                                                       |

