| Probable/definite    | grade 3     | yes                            | stop (for the affected patient but others to continue)                                                                                    |
| Probable/definite    | grade 3     | no                             | Stop for all patients                                                                                                                     |

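### The Part 2 dose is the average of the doses tolerated in section 6.1.1 but of the doses reached in section 9.2.2, and no text says which dose counts for a patient stopped in Part 1

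*Protocol*

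**What the plan says.** All references are to the protocol.

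- **Section 6.1.1 (Dose escalation)** sets the Part 2 dose: "the average of the three maximum tolerated doses by the three patients will be defined as MSD for part 2". The next sentence gives the aim: "we aim to find the highest dose that generates, if any at all, at maximum only transient mild/moderate AEs".
- **Section 9.2.2 (Assessment of secondary outcomes)** gives the calculation again, in other words: "MSD is calculated as the average dose from all maximally reached doses by the 3 patients in the dose escalating part of this trial". Section 5.2 lists the MSD among the secondary outcomes.
- **The synopsis** gives as a secondary objective: "Determination of the maximal suitable dose based on safety profile and preliminary efficacy". Section 8.1.1 (Part 1) likewise ties the MSD to the seriousness, intensity and causality of adverse events (AEs), and refers to section 8.3.
- **Section 8.3 (Dose modifications)** says when a Part 1 patient escalates, is delayed or stops. A grade 4 event with a causal link to TLN counts as unacceptable toxicity and "will lead to a stop of treatment without resuming the treatment in the affected patient". In the Part 1 table, other related events stop only the affected patient, and one row reads "Stop for all patients".
- **Section 6.1.3** lets Part 1 patients continue at their own MSD or at dose level 14.
- **Section 8.1.1 (Part 2)** gives the MSD to nine patients once a week for eight weeks.

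**The concern.** A patient taken off treatment because of a grade 3 event at 360 mg has reached 360 mg but, in ordinary usage, has not tolerated it. Sections 6.1.1 and 9.2.2 would therefore enter different numbers for that patient. Neither term is formally defined. Section 8.3, to which section 8.1.1 sends the reader, lists actions only. It does not say whether a stopped patient's value is the dose that caused the stop or the level below it.

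Taken literally, section 9.2.2 counts the dose that caused the stop, even one followed by a related grade 4 event. That conflicts with the aim in section 6.1.1. A grade 3 or 4 event is more than moderate, and a grade 2 event still present at the next infusion is not transient in the sense of the section 8.3 table.

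At stake is the dose for nine new patients in the first human trial of TLN. The two wordings part company only after a Part 1 patient has been stopped, which is when an unambiguous rule is needed. The rule sets a dose given during the trial, so it belongs in the protocol and cannot be left to the analysis plan.

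**Working it through.** The protocol states no numerical MSD, so there is no figure to reproduce. The check compares the two rules on the planned dose levels.

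**Inputs**

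- Dose levels (section 8.1.1): 6, 12 and 60 mg, then steps of 60 mg up to 720 mg, 14 levels in all.
- Three patients, arithmetic mean (sections 6.1.1 and 9.2.2).
- Assumption: a stopped patient's *tolerated* dose is one level below the stopping dose.
- A patient who completes the escalation counts as 720 mg under both rules.
- The stopping doses below are illustrative.

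**Gap per stopped patient** = (stopping dose − level below) / 3

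- Stopped at 120 mg or above: 60 / 3 = 20 mg.
- Stopped at 60 mg: (60 − 12) / 3 = 16 mg.
- Stopped at 12 mg: (12 − 6) / 3 = 2 mg.
- Stopped at 6 mg, with the level below taken as 0 mg: 6 / 3 = 2 mg.
- Largest possible gap: 3 × 20 = 60 mg.

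**MSD under the two rules**

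| Part 1 result | Reached (9.2.2) | Tolerated (6.1.1) | Gap |
|---|---|---|---|
| Nobody stopped | 720 mg | 720 mg | 0 |
| One stopped at 720, two complete 720 | (720 + 720 + 720) / 3 = 720 mg | (660 + 720 + 720) / 3 = 700 mg | 20 mg |
| One stopped at 480, two complete 720 | (480 + 720 + 720) / 3 = 640 mg | (420 + 720 + 720) / 3 = 620 mg | 20 mg |
| Two stopped at 480, one completes 720 | (480 + 480 + 720) / 3 = 560 mg | (420 + 420 + 720) / 3 = 520 mg | 40 mg |
| All three stopped at 360 | 1080 / 3 = 360 mg | 900 / 3 = 300 mg | 60 mg |
| All three stopped at 60 | 180 / 3 = 60 mg | 36 / 3 = 12 mg | 48 mg |

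Two rows stand out. When all three stop at the same level, the section 9.2.2 wording gives the Part 2 patients the very dose that stopped every Part 1 patient. When one patient stops at 720 mg and the other two complete it, that wording gives 720 mg, the same as if nobody had stopped.

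**The case against.** The strongest reply is that the context already settles the matter. Section 6.1.1 also states the calculation, does so in the design section, and is the text that fixes the dose for Part 2. Section 9.2.2 is one line in a list of outcome assessments. The aim in section 6.1.1, the link to AE severity and causality in section 8.1.1, and the label of unacceptable toxicity in section 8.3 all point to *tolerated*. So does section 6.1.3: on the *reached* reading, the personal MSD of a stopped patient would be the dose that stopped that patient.

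The effect is also bounded at one dose step. Safeguards exist: unanimous decisions of the Internal Monitoring Committee (section 1.6), a DSMB meeting after the MSD is defined (section 1.7), and individual stopping rules in Part 2 (section 8.3).

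Most of this stands. It shows which reading is probably meant, and it limits the harm. It does not supply the missing rule. The aim is a goal, not a way to assign a value to each patient, and two current sections still use words that give different doses.

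A reader might infer two stronger points that the documents do not support:

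- **That section 9.2.2 governs, so that the trial is set to treat Part 2 patients at a toxic dose.** Nothing ranks section 9.2.2 above section 6.1.1, and the context runs the other way.
- **That averaging is itself an error.** Even on the *tolerated* rule, one stop at 360 mg with two completers gives (300 + 720 + 720) / 3 = 580 mg, above the dose that stopped one patient. But averaging individual limits is an openly stated design choice, and 580 mg is below what the other two tolerated. How the MSD is reviewed may be covered in the DSMB charter, which is not shown.

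**Conclusion.** The inconsistency is real and should be fixed. Sections 6.1.1 and 9.2.2 describe the Part 2 dose in terms that differ once a Part 1 patient is stopped for a TLN-related event, and the protocol does not say which dose then counts. The context favours *tolerated*, so this is a conflict of wording with a missing definition and not evidence that a toxic dose is intended.

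The size is 20 mg per patient stopped at 120 mg or above, less at the lower levels, at most 60 mg, and nil if nobody is stopped. These figures rest on taking *tolerated* as one level below the stopping dose, which the protocol does not state. How likely a stop is cannot be judged from the document.

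**What to change.** In section 9.2.2, replace *maximally reached doses* with *maximum tolerated doses*. In both section 6.1.1 and section 9.2.2, define a patient's maximum tolerated dose as the highest dose level that the patient received and that led to neither of the following:

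- permanent discontinuation of that patient for a TLN-related AE (possible, probable or definite) under section 8.3;
- withdrawal of that patient under section 7.3 because such an AE delayed treatment by more than three weeks.

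The definition should also say what is entered for a patient stopped at 6 mg, where there is no lower level; 0 mg is the natural value.

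A shorter definition by any stop under section 8.3 would not do, for two reasons. A possible grade 2 event that never resolves can end in withdrawal under section 7.3 without a rechallenge, and that dose would still count as tolerated. Section 8.3 also stops patients for most SAEs with no causal link to TLN. Those patients are replaced, as are patients who drop out for unrelated reasons (section 6.1.1), so their stops should not lower the MSD.

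The cost is one changed term and one definition in two sections, with no extra data or visits. The downside is that the Part 2 dose may be up to one dose step (60 mg) lower than under the section 9.2.2 wording.
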